### Sample size calculation

The sample size calculation is based on a non-inferiority design, i.e., on the hypothesis that nonoperative management is non-inferior to operative management. As stated before the EQ-5D will serve as primary outcome measure. We have used the results from earlier studies on proximal femoral fracture treatment in the elderly for the sample size calculation [51–53]. Assuming a two-sided significance level (alpha) of 0.05 and a power of 80% with a standard deviation (s) of 0.30 on the EQ-5D utility score and a noninferiority limit (d) of 0.15 (which equals 0.5 SD), a total of 50 subjects are needed in each treatment arm. Taking into account a rate of 60% loss to follow-up and mortality until 3 months, a total number of 160 participants has to be recruited.

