### Statistical analysis

Data will be analyzed using the Statistical Package for the Social Sciences (SPSS) version 24.0 or higher (SPSS, Chicago, Ill., USA) and will be reported following the STrengthening the Reporting of OBservational studies in Epidemiology (STROBE) guidelines. Normality of continuous data will be tested with the Shapiro-Wilk test. Homogeneity of variances will be tested using the Levene’s test. A two-sided *p*-value < 0.05 will be taken as threshold of statistical significance in all statistical tests. The analysis will be performed on a per-protocol basis, (as that is the most conservative approach) and verified by an intention-to-treat analysis if needed. Patients who have died will remain in the analysis as censored. If necessary, missing values will be replaced using multiple imputation following the predictive mean matching method, using ten imputations.

Descriptive analysis will be performed in order to report the outcome measures and other variables collected for the entire population as well as per treatment group. Continuous data will be reported as mean and SD (if Normal) or median and quartiles (if non-Normal), categorical data as number with percentage.

Univariate comparison between the groups will be done using Student’s T or Mann-Whitney U-test (for Normal and non-Normal data, respectively), or Chi-squared test or Fisher’s Exact test (categorical data, as applicable). The Student’s T-test will be done with equal variance assumed or not assumed, based upon the results of the Levene’s test.

For the primary outcome measure, a non-inferiority margin of 0.15 points for mean EQ-5D scores was chosen because it is reasonable and on the border of what would be considered a clinically important effect. The null hypothesis in the non-inferiority framework is that nonoperative management is inferior to operative management with regards to the EQ-5D score. This hypothesis will be tested through the adjusted contrast between the two interventions at 6 months. Specifically, the 95% confidence interval of the estimated contrast will be examined, and if the limit of the interval is less than the threshold value of 0.15 points, non-inferiority of nonoperative management to operative management at 6 months will be concluded.

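### The 50 evaluable patients per arm match a one-sided 5% test; under the stated two-sided 5% level and the 95% CI rule they give about 70% power, not 80%

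*Protocol article*

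**What the plan says.** The Sample size calculation section describes a non-inferiority design with EQ-5D as the primary outcome. It opens the calculation with "Assuming a two-sided significance level (alpha) of 0.05 and a power of 80" per cent, adds a "standard deviation (s) of 0.30 on the EQ-5D utility score" and a margin of 0.15, described as half a standard deviation, and concludes that "a total of 50 subjects are needed in each treatment arm". It mentions no one-sided level and no variance reduction from covariates or repeated measurements.

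The Statistical analysis section sets a two-sided 5% threshold for every test. The decision rule for the primary outcome at 6 months reads: "the 95% confidence interval of the estimated contrast will be examined, and if the limit of the interval is less than the threshold value". That threshold is set at 0.15, and meeting the condition leads to a conclusion of non-inferiority. Just before this it gives the null hypothesis: nonoperative management is inferior to operative management on EQ-5D. The outcome section says that lower utility scores mean poorer quality of life.

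**The concern.** A sample size should follow from its stated inputs and belong to the test that will be used. Here the significance level in the sample size text and the confidence level in the analysis text agree with each other, but neither agrees with 50 per arm. If 50 was derived at a more lenient level than the one applied at analysis, the stated 80% power is wrong. The chance of failing to show non-inferiority when the treatments are truly equal would then be about 30% instead of 20%, before any loss to follow-up or death.

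There is a smaller point in the same decision rule. It refers to the limit of the interval without saying which one, and to the contrast without saying which arm is subtracted from which. The primary conclusion rests on that sentence, so it should allow only one reading.

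**Working it through.** **Inputs.** From Sample size calculation: SD 0.30, margin 0.15, power 80% (z = 0.8416), two-sided alpha 0.05, equal arms. From Statistical analysis: a 95% confidence interval compared with the margin. Setting one limit of a 95% interval against a margin is a one-sided 2.5% test (z = 1.960). The protocol gives no expected difference, so a true difference of 0 is assumed.

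**Formula.** n per arm = 2 × (z_alpha + z_power)² × (SD / margin)². With SD / margin = 0.30 / 0.15 = 2, this is n = 8 × (z_alpha + 0.8416)².

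**Reproducing the protocol's 50.**
- One-sided 5% (z_alpha = 1.645): 8 × (2.4865)² = 49.5, so 50 per arm. This matches the protocol.

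**With the inputs as stated.**
- Two-sided 5% (z_alpha = 1.960): 8 × (2.8016)² = 62.8, so 63 per arm. By the noncentral t distribution, 63 gives 79.5% and 64 gives 80.1%, so 64 with a t correction.
- 63 / 50 = 1.26, that is 26% more evaluable patients per arm than stated.

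**Power with 50 evaluable per arm.**
- Standard error = 0.30 × √(2/50) = 0.06, and 0.15 / 0.06 = 2.5.
- 95% interval: Φ(2.5 - 1.960) = Φ(0.540) = 70.5% (69.7% by noncentral t).
- 90% interval: Φ(2.5 - 1.645) = Φ(0.855) = 80.4% (79.9% by noncentral t).

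**Other possible origins of 50.** A two-sided equivalence calculation (two one-sided tests at 5%, 80% power) gives 8 × (1.645 + 1.2816)² = 68.5, so 69 per arm, and does not explain it. Covariate adjustment would bring 62.8 down to 50 only with a variance reduction of 1 - 50/62.8 = 20%. The sample size text claims none.

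**The decision rule.** Take operative minus nonoperative and use the upper limit: a limit below 0.15 then correctly excludes a loss of 0.15 or more under nonoperative care. Take nonoperative minus operative and apply the same words: an interval from -0.42 to -0.18 meets them although it shows harm beyond the margin. The sentence does not say which is meant.

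**The case against.** - **The planned analysis is not the simple test.** The primary analysis is an adjusted longitudinal GEE, and arm sizes are set by shared decision-making, so 1:1 is nominal. This stands as a caution: 70% is the power of the simple formula, and the planned model could do better or worse. It does not rescue 50, because the protocol claims no efficiency gain and an unequal split of the same total raises the standard error.
- **The error is in the safe direction.** A reader might infer that the mismatch makes a false claim of non-inferiority more likely. It does not: the 95% interval is the stricter rule, and the cost is power alone.
- **The direction is clear from context.** The null hypothesis and the positive margin do fit the upper limit of operative minus nonoperative, which is the natural reading. A reader might go further and infer that the rule could be passed whatever the data show. That is not so: even on nonoperative minus operative, an interval from -0.05 to 0.20 has an upper limit above 0.15 and fails. What stands is a wording gap.
- **The recruitment total.** A reader might charge the whole recruitment shortfall to this point. The step from 100 evaluable to 160 recruited (100 × 1.6) is a separate question about attrition and is not counted here.

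**Conclusion.** The point holds. The stated inputs require 63 evaluable patients per arm (64 with a t correction), and 50 belongs to a one-sided 5% level that appears nowhere in the protocol. With 50 evaluable per arm and the 95% interval, power is about 70%, roughly 10 percentage points below the stated figure. This assumes a true difference of 0, SD 0.30, equal arms and a simple two-sample comparison. If nonoperative care is truly somewhat worse, power is lower. The type I error of the decision rule is unaffected. The unnamed limit and direction are a secondary wording correction.

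**What to change.** Keep the 95% confidence interval rule. In Sample size calculation, state that 50 evaluable patients per arm gives approximately 70% power at two-sided 5% with SD 0.30, margin 0.15 and no true difference, and that 80% would need about 63 per arm.

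In Statistical analysis, reword the rule: non-inferiority is concluded if the lower limit of the two-sided 95% confidence interval for the adjusted mean EQ-5D difference (nonoperative minus operative) is above -0.15.

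The cost is two sentences and a less favourable stated power. Raising the target to 63 per arm would mean enrolling more patients in a study under way since September 2018; the correction does not depend on that.

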Guidelines have no strict advice for frail elderly with a proximal femoral fracture, as a result of lack of evidence on palliative care in these patients. The National Institute for Health and Care Excellence (NICE) advises to discuss if patients are open to hospital admission and possible surgery [14]. Dutch guidelines advocate operative treatment in patients with a life expectancy beyond 6 weeks [2, 15]. This leads to practice variation. Current practice is that over 90% of femoral fracture patients that presented to hospital are operated, even if they are institutionalized and have a limited life expectancy [16].

A systematic review of the literature on nonoperative management versus operative management of proximal femoral fractures in frail elderly resulted in 7 studies that met the eligibility criteria [17–24]; All were nonrandomized, five were retrospective studies. A total of 1189 patients were included, 242 (20.3%) were treated nonoperatively. The mean age ranged from 76.9–101.8 years. The data indicated an unadjusted pooled odds ratio of 3.95-fold and 3.84-fold higher 30-day and 1-year mortality for nonoperative versus operative management. Data also showed that mortality was affected by the number of comorbidities. None of the comparative studies examined (health-related) quality of life, degree of frailty, and costs. The literature review shows a lack of high quality evidence on the true effect of nonoperative versus operative management on quality of life, pain, mortality, complications, and costs in the first 6 months after trauma in frail institutionalized elderly. Those answers are needed to aid patients and health care providers in decision-making for surgical repair, particularly in frail elderly patients. The above shows that the best treatment is not known, and supports the need for high quality evidence. Evidence supporting (non)operative management in terms of quality of life, pain, complications, and mortality is lacking.

It is common practice to decide on treatment following a shared decision process, but still nonoperative treatment is uncommonly used. It is unclear to what extent patients or their relatives currently have a say in the treatment decision.

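### The recruitment target of 160 is 100 × 1.60; the plan's own 60% attrition needs 100 / 0.40 = 250, and 160 leaves about 32 patients per arm instead of 50

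*Protocol article*

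**What the plan says.** All of the relevant figures are in the protocol article, under Sample size calculation:

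- Error level and power: "Assuming a two-sided significance level (alpha) of 0.05 and a power of 80" percent.
- Variability: "a standard deviation (s) of 0.30 on the EQ-5D utility score".
- Margin: "a noninferiority limit (d) of 0.15 (which equals 0.5 SD").
- Resulting size: "a total of 50 subjects are needed in each treatment arm", so 100 in total.
- Allowance for attrition: "a rate of 60% loss to follow-up and mortality until 3 months, a total number of 160 participants has to be recruited".

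No other adjustment is given between the 100 evaluable patients and the 160 to be recruited. Under Statistical analysis, non-inferiority is judged from the 95% confidence interval of the adjusted treatment contrast at 6 months, and patients who die are treated as censored. Under Study design and setting, the study is non-randomized and no ratio between the arms is fixed. The Background reports that in the review of earlier comparative studies "242 (20.3%) were treated nonoperatively".

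**The concern.** An allowance for attrition must return the required number after the losses are taken out. Here it does not: removing 60% of 160 leaves well short of 100. The full chain of inputs and the result are printed in the article, so this is an error in a stated figure and not a detail left to a fuller document.

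At stake is the power of the primary non-inferiority test. If the number analysed is about a third below the number the calculation requires, the claimed 80% does not describe this study. A result that fails to show non-inferiority could then easily arise even when the two strategies give the same quality of life, and the Discussion says the results may feed into treatment guidelines.

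The target is also only a total. Treatment is chosen through shared decision-making, so the split is not under the investigators' control, and the smaller arm largely determines the precision.

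**Working it through.** **Inputs.** SD 0.30, margin 0.15, power 80%, 50 per arm, 60% attrition and a target of 160, all from Sample size calculation. True difference 0 and equal arms are assumed unless stated otherwise. Power uses the normal approximation for a two-sample comparison of means.

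**1. Reproduce the 50 per arm.** n = 2 × [SD × (z₁₋α + z₀.₈₀) / margin]²

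- One-sided 5%: 2 × [0.30 × (1.645 + 0.842) / 0.15]² = 49.5, rounded up to 50. This matches.
- One-sided 2.5% (two-sided 5%): 2 × [0.30 × (1.960 + 0.842) / 0.15]² = 62.8, rounded up to 63. This does not match.

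**2. Reproduce the 160.**

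| Method | Result |
|---|---|
| 100 × (1 + 0.60) | 160 (exact match) |
| 100 / (1 − 0.60), correct inflation | 250 |
| 100 / 0.60, reading 60% as retention | 167 |

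Attrition at which 160 would be right: 1 − 100/160 = 37.5%. The document does not give that rate.

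**3. What 160 delivers at 60% attrition.** 160 × 0.40 = 64, or 32 per arm.

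**4. Power with 32 per arm.** SE = 0.30 × √(2/32) = 0.075, and margin/SE = 0.15/0.075 = 2.0.

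- One-sided 5%: Φ(2.0 − 1.645) = 0.639, about 64%.
- 95% CI rule: Φ(2.0 − 1.960) = 0.516, about 52% (50% with the t distribution).

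**5. Unequal arms (illustrations, same 64 evaluable, 95% CI rule).** SE = 0.30 × √(1/n₁ + 1/n₂).

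| Nonoperative share | Evaluable arms | SE | Power |
|---|---|---|---|
| 50% | 32 vs 32 | 0.075 | 52% |
| 35% (assumed) | 22 vs 42 | 0.079 | 48% |
| 20.3% (earlier studies, Background) | 13 vs 51 | 0.093 | 36% |

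At a share of 20.3%, 160 recruits include only 160 × 0.203 ≈ 32 nonoperative patients before any loss.

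**The case against.** Nobody can make 160 follow from 100 and 60% by a valid route, but several points bear on the size of the problem.

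- *The analysis uses more than the completers.* The primary model is a GEE over five visits, corrected for baseline differences, with multiple imputation if necessary. This may change precision in either direction, so the power figures above are approximations. However, the sample size section claims no such gain, and the non-inferiority decision is tied to the 6-month contrast. The section itself counts deaths as losses.
- *The figure 250 is conditional.* It takes the plan's 50 per arm as given. Under the 95% CI rule, 50 per arm gives Φ(2.5 − 1.960), about 70% power; 80% would need 63 per arm, or 126 / 0.40 = 315 recruits. This stands. The attrition error alone takes power from 80% to 64%; the further drop to 52% comes from the mismatch between the one-sided 5% behind the 50 and the interval rule used for the decision.
- *The unequal splits are not forecasts.* The 20.3% comes from earlier nonrandomized studies, and the structured decision process may raise it; the 35% is an assumption. Both only show the direction. The finding does not depend on them.
- *A recruitment count per arm cannot be guaranteed in an observational cohort.* True, but the evaluable number per arm can still be the stated aim, as it already is for the 50.

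**Conclusion.** The concern holds. Given the plan's 50 per arm and 60% attrition, the number to recruit is 250; the stated 160 is 90 short and matches only an invalid inflation. With 160, at most 64 patients are expected to be observed, 32 per arm if the arms and the losses are equal. The 64 is an upper bound for the primary time point, because the 60% runs only to 3 months and the test is at 6 months.

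The like-for-like power is about 64%, against 80% stated. Under the decision rule actually planned it is about 52%, so with equal arms and truly identical outcomes the study would fail to show non-inferiority about half the time, and more often if the arms are unequal. These figures rest on SD 0.30, margin 0.15, no true difference and a two-sample comparison of observed patients. The arithmetic error itself rests on no assumption beyond the plan's own figures.

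**What to change.** Correct the last sentence of Sample size calculation in one of three ways:

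1. State 250 as the number that 60% attrition requires for 50 evaluable patients per arm.
2. Keep 160 and state what it delivers at 60% attrition: about 32 evaluable per arm with equal arms, and about 52% power under the 95% CI rule (64% at one-sided 5%), noting that losses between 3 and 6 months would reduce this further.
3. Keep 160 and justify attrition of 37.5% in place of 60%.

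In each case, express the recruitment target in terms of evaluable patients per treatment arm, and say what split between the arms is assumed. If option 1 is chosen, state the error level behind the 50, since 250 does not give 80% power under the 95% CI rule.

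Options 2 and 3 are changes of wording with no extra patients; under option 2 the stated power becomes less favourable. Only option 1, if acted on, means recruiting 90 more patients.

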### Data management and monitoring

Data will be encoded and stored in a pass-word protected database with restricted access to the researchers only. Data will be entered once. Quality of the entered data will be monitored by checking entry for a random sample of patients prior to database locking.

## Discussion

Treatment guidelines for proximal femoral fractures are mainly focused on regaining function and independence in activities of daily living. Other considerations may apply to frail elderly with a limited life expectancy, for whom comfort and pain are particularly relevant. Whether or not operative treatment is needed in this respect is undecided. This study aims to investigate the value of nonoperative management versus operative management of proximal femoral fractures in a selected group of frail institutionalized elderly with a limited life expectancy.

There are some limitations to this study. First, selection bias could be a factor in this study, since patient or proxy opting for nonoperative management may arguably be in worse condition with regards to their pre-trauma condition and comorbidities. A randomized controlled trial (RCT) would have avoided selection bias, however randomizing patients with a limited life expectancy was considered unfeasible (and unethical) by the research team. Patient recruitment in trials randomizing between operative and nonoperative treatment is known to be challenging, and would likely introduce an unacceptably high level of selection bias; surgeons with clear preference for a particular treatment may be unwilling to inform patients about the study, and patients (or their proxy if patient is unable to decide) with preference for a particular treatment will not sign informed consent. The chosen observational design allows all centers and all patients to participate, and real-life data will be collected. For patients with severe cognitive impairment, informed consent will be obtained by their health care proxy. That makes the current study design the most feasible to investigate this issue. As a second limitation, it could be argued that the questionnaire completed by proxy may differ from the patients rating, however since the majority of this study population is expected to suffer from cognitive impairment, questionnaire completion by proxy will be inevitable. Finally, at least 26 hospitals will participate, and treatment protocol and shared decision processes may vary across sites. This may introduce some heterogeneity, but also makes the results more generalizable.

To the best of our knowledge, this is the first comparative study that addresses this issue with regard to quality of life and cost-effectiveness and also the first study to provide detailed information about nonoperative management with a longer term follow-up in frail patients with a proximal femoral fracture. This study will contribute widely to the current knowledge about the process of nonoperative management, treatment satisfaction with patients, proxy and caregivers in this select group of frail hip fracture patients in the context of quality of life. The results of this study may be used for updating the Dutch national “Guideline for the treatment of proximal femoral fractures” (set out by the Dutch Association of Surgery and the Dutch Orthopaedic Association) and the Dutch national “Guideline for multidisciplinary treatment of vulnerable elderly treated operatively” (set out by the Dutch Association of Clinical Geriatrics), but may also help updating international treatment guidelines on proximal femoral fractures. The results could be further used in the context of advanced care planning and expectation management and therefore aid treatment decision making in future frail hip fracture patients.

## Data Availability

Not applicable.

## Abbreviations

ADL: Activities of daily living
ASA: American Society of Anesthesiologists
BMI: Body Mass Index
CCI: Charlson Comorbidity Index
CT: Computated Tomography
ED: Emergency Department
EQ-5D: EuroQoL-5D
FAC: Functional Ambulation Category
GCP: Good Clinical Practice
GEE: Generalized estimating equations
ICER: Incremental Cost-Effectiveness Ratio
iMCQ: Medical Consumption Questionnaire
iMTA: Institute of Medical Technology Assessments
MTREC: Medical Research Ethics Committee
NICE: National Institute for Health and Care Excellence
NOV: Dutch Orthopaedic Association
NVKG: Dutch Association of Clinical Geriatrics
NVOT: Dutch Association of Orthopaedic Surgery
NVT: Dutch Association of Trauma Surgery
NVvH: Dutch Association of Surgery
PACSLAC: Pain Assessment Checklist for Seniors with Limited Ability to Communicate
PACSLAC-D: Pain Assessment Checklist for Seniors with Limited Ability to Communicate - Dutch language version
PFN: Dutch Patient Federation
QALY: Quality Adjusted Life Years
QODD: Quality of Dying and Death
QoL: Quality of Life
SD: Standard Deviation
SDM: Shared Decision Making
SPSS: Statistical Package for the Social Sciences
STROBE: STrengthening the Reporting of OBservational studies in Epidemiology
VERENSO: Association of Elderly Care Physicians
WHO: World Health Organization
WMO: Medical Research Involving Human Subjects Act (in Dutch: Wet Medisch-wetenschappelijk Onderzoek met Mensen
